#### Health behaviors (objective 2c)

*Level of physical activity*: This parameter will be assessed with the validated French version of the International Physical Activity Questionnaire—Short Form [91]. This data will be used to determine if patients are following the recommendations of the American Heart Association regarding exercise, which are: at least 30 min (minimum 5 days per week) of moderate intensity aerobic activity such as brisk walking [10].

*Smoking status*: This variable will be assessed using the validated self-report items developed by Statistics Canada to assess the current smoking status (non-smoking, occasional smoker, smoking every day) [92] in the 30 days preceding each time point.

*Alcohol use*: The patients’ compliance with recommendations regarding alcohol consumption (≤ 1 drink/day for women and ≤ 2 drinks/day for men) [7, 8, 10, 93, 94] will be assessed with the first 3 items of the validated French version of the Alcohol Use Disorders Identification Test [93, 94]. These items are well validated and are highly correlated with objective measures of alcohol consumption [95].

*Fruit and vegetable intake*: Patients usual consumption of fruit and vegetables will be assessed using the 6-item Fruits and Vegetables Questionnaire [96]. This brief measure is predictive of overall eating habits.

#### Quality of life and psychological distress (objective 2d)

*Health-related quality of life*: The validated French version of the 12-item Short-Form Health Survey Version 2 will be used to assess the health-related quality of life of patients [97, 98]. The physical summary score and mental summary score will be used in the current study.

*Psychological distress*: Anxiety and depressive symptoms will be measured with the validated French version of the Hospital Anxiety and Depression Scale [99, 100]. The internal consistency of the questionnaire and its 2 subscales (anxiety and depression) is well established (α = 0.68–0.93) [101]. The total score will be used as a measure of overall psychological distress in the current study. Heart-focused anxiety will be assessed with the French version of the Cardiac Anxiety Questionnaire [102, 103]. It has good internal consistency (α ≥ 0.83) and satisfactory convergent validity [102].

#### Other variables and measures

*Sociodemographic data*: Sociodemographic information, including employment status, educational level and family income (i.e. socio-economic status), will be obtained using a brief questionnaire.

*Medical comorbidities and cardiovascular risk factors for CAD*: This data will be obtained through a medical interview and review of medical records. Obesity will be assessed using body mass index (kg/m^2^), which will be computed from the reported height and weight of patients obtained during the medical interview. The Charlson Comorbidity Index will be used to summarize the patients’ medical comorbidities [104, 105].

#### Other psychosocial risk factors for CAD

Social support will be assessed with the validated French version of the Modified Medical Outcomes Study Social Support Survey. This brief measure assesses the patients’ perceived social support and has good internal consistency (α = 0.85–0.88).Depression, agoraphobia, health anxiety and somatic symptom disorder will be assessed with the ADIS-5 which presents good to excellent inter-rater agreement for these psychiatric diagnoses [106].Post-traumatic stress disorder (PTSD) will be assessed using the French version of the PTSD Checklist for DSM-5, a 20-item self-report measure that assesses symptoms of post-traumatic stress disorder [107, 108].Sleep habits and sleeping problems will be assessed by using the French version of the Pittsburgh Sleep Quality Index [109, 110]. The brief self-reported questionnaire has good internal consistency (α = 0.70–0.83) and test–retest reliability [109].

### Procedures

#### Recruitment and assessment of patients

Research assistants at the recruitment site will identify potentially eligible patients by consulting medical files. They will subsequently present them the consent form, explain the research project, answer questions and, upon acceptance, administer the medical interview, the fruits and vegetables intake measure and the physical activity measure. Face-to-face or phone assessments with a trained interviewer (doctoral student in psychology) to administer the selected modules of the ADIS-5 will be scheduled onsite with the consenting patients. Patients will fill out the questionnaires right after the face-to-face interview in an electronic format with assistance from a research assistant if needed. Patients who are unable to come in for a face-to-face interview (either due to their medical condition or to distance from the recruitment site) will be offered to complete the interview by phone and to fill out the questionnaires online through the REDCap secure web-based application [111], by phone or by regular mail. For regular mail and website completion, patients will receive a follow-up call to offer assistance a week after the questionnaires are sent. All measures will be administered at all time points. Patients will be contacted  two weeks before each time point in order to schedule the interview (onsite or by phone) and questionnaire completion (electronic format, paper or by phone). Patients who are unreachable after three weeks will be considered lost to follow-up. At each time point, research personnel, blinded to the patients’ results to the ADIS-5, will review the medical records of all patients. To improve retention, patients will have a chance to win an electronic tablet for the completion of each time point (interview and questionnaires) as a compensation for their time.

#### Quality control

Assessors (psychology doctoral students who completed ≥ 180 h of academic courses and practicums focusing on clinical assessment) will receive initial training (14 h) and subsequent weekly clinical supervision. The ADIS-5 interviews will be audio-recorded to facilitate supervision and to realize inter-rater agreements on the diagnoses. Inter-rater agreements on all ADIS-5 interviews and data will be established using a random sample of 25% of all files reviewed and all ADIS-5 interviews realized at each time point. All questionnaires and interviews will be reviewed after completion and patients will be contacted if missing data are present. Finally, most of the questionnaires will be filled out electronically, reducing the risk of incorrect or missing data.

### Statistical analyses

All study data will be collected and managed using the REDCap data capture tools [111]. For objective 1, the prevalence and incidence of GAD and PD will be presented with their 95% confidence intervals for each time point. As a sensitivity analysis, the stability of baseline diagnoses of PD and GAD will be assessed at the 3-month follow-up. Diagnoses will be considered stable if less than 10% of patients experience remission (no longer meeting the diagnostic criteria for PD or GAD) between these time points. If this criterion is not fulfilled, all analyses for objective 2 will be repeated using the diagnoses established at the 3-month follow-up to identify patients with and without PD or GAD. Inter-rater agreements on ADIS-5 diagnoses will be assessed by computing Cohen’s Kappa and its 95% confidence interval.

In the context of objective 2, generalized linear mixed models (continuous outcomes) and generalized estimating equation models (dichotomous outcomes) with group X time interactions will be used to compare the evolution of both groups (with and without GAD or PD) in terms of adverse cardiac events, adherence to treatments (cardiac rehabilitation, pharmacotherapy), CAD-related health behaviors, quality of life and psychological distress All models will be adjusted for age, sex, cardiovascular risk factors, medications and medical comorbidity. Additional control variables will include, when relevant: diagnosis of depression, PTSD symptoms, previous cardiac events and interventions, health behaviors and social support. In the presence of significant effects of PD or GAD, analyses will be repeated in order to explore differences among men and women (group X sex X time).

As an exploratory measure, analyses will be repeated separately for GAD and PD. All analyses will be repeated using 3 groups (patients with PD or GAD at baseline, patients who developed PD or GAD afterwards, patients without PD or GAD at all time points) in order to explore the impact of developing GAD or PD over time.

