### Possible mechanisms linking panic disorder and generalized anxiety disorder with CAD prognosis

Though still unclear, physiological and behavioral pathways have been proposed to explain how anxiety disorders and CAD influence each other and subsequently lead to poorer outcomes. Part of the association between CAD and anxiety disorders may be explained by physiological factors, such as increased inflammation [20, 21, 36, 39, 58]. Anxiety disorders are also associated with higher rates of hypertension, obesity, diabetes and dyslipidemia, which all increase the cardiovascular risk [21, 29, 59]. PD and GAD have also been linked to poorer health behaviors [20, 21, 36, 60–64]. For instance, the likelihood of alcohol use disorder, either dependence or abuse, is 79–83% higher in patients with GAD or PD than in patients without these disorders [65, 66]. These anxiety disorders are also associated with a 50–90% increased risk of daily smoking and nicotine dependence as well as low levels of physical activity [61, 63, 64, 67–70]. Furthermore, high levels of anxiety have been associated with non-attendance and non-completion of cardiac rehabilitation programs and non-adherence to cardiac medication [64, 70–75]. Consequently, another part of the association between anxiety disorders and CAD could be explained by the negative influence of these disorders on health behaviors and adherence to evidence-based risk-reducing recommendations and treatments for CAD [20, 21, 56, 64, 70, 75].

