#### Justification of sample size

The minimal sample sized required for each objective was calculated separately. The final sample size was established according to the objective requiring the highest number of participants (i.e. objective 2a, n = 2527 participants). That estimation was based on a previously reported rate of adverse cardiac events of 14.3% [22]. Considering an anticipated attrition rate of 30% after 2 years, a total of 3610 patients will have to be initially recruited. Based on the lower range of findings from studies of GAD in patients with CAD, the relative risk of adverse events in patients was conservatively estimated at 1.50 [33]. This data was used in the absence of similar studies in patients with PD.

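### With 30% attrition planned, the visit-by-visit PD/GAD prevalence and incidence are unbiased only if retention is unrelated to diagnosis, and a larger sample does not cure this

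*Protocol article*

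**What the plan says.** All references are to the Protocol article.

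- **Objective 1** (Statistical analyses): "the prevalence and incidence of GAD and PD will be presented with their 95% confidence intervals for each time point". Under Presence of PD and GAD, both diagnoses come from the ADIS-5 interview at each of the five time points.
- **Objective 2, dichotomous outcomes** (Statistical analyses): "generalized estimating equation models (dichotomous outcomes) with group X time interactions will be used to compare the evolution of both groups". Continuous outcomes get mixed models. On covariates: "All models will be adjusted for age, sex, cardiovascular risk factors, medications and medical comorbidity". Depression, PTSD symptoms, previous cardiac events, health behaviours and social support are added where relevant.
- **Attrition** (Justification of sample size): "Considering an anticipated attrition rate of 30% after 2 years, a total of 3610 patients will have to be initially recruited". The 30% is used nowhere else.
- **Missing data** (Quality control): questionnaires and interviews are checked and patients recontacted. Under Recruitment and assessment of patients, someone who cannot be reached for three weeks counts as lost, while the medical records of all patients are reviewed at each time point.
- **Sensitivity analysis**: the only one named concerns the stability of baseline diagnoses at 3 months.
- **Background** (Possible mechanisms): "high levels of anxiety have been associated with non-attendance and non-completion of cardiac rehabilitation programs and non-adherence to cardiac medication".

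**The concern.** A proportion computed at a visit among those who attend it contains no covariates. It equals the cohort proportion only if attending is unrelated to having the diagnosis at that time. Recruiting 3610 instead of 2527 restores the number interviewed at 2 years but not their representativeness. If cases and non-cases are retained differently, the larger sample only narrows the interval around a shifted value.

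Record review cannot repair this for objective 1, because the diagnosis exists only where there was an interview. Incidence is exposed in the same way: a patient who develops PD or GAD and then stops responding is never counted.

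Prevalence and incidence form one of the two main objectives, and the Discussion expects the data to inform decisions on systematic screening. A biased 24-month figure with a tight interval would be a poor basis for that.

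The dichotomous outcomes of objective 2 raise a related but narrower question. Likelihood-based mixed models tolerate dropout that depends on earlier observed outcomes. Standard GEE tolerates dropout that depends on modelled covariates, but not in general on earlier outcomes. The two outcome types therefore rest on different missing-data assumptions.

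**Working it through.** **The plan's own figure.** 2527 / (1 − 0.30) = 3610. It reproduces, so about 2527 patients are expected to have 2-year data.

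**Prevalence.** Let p be the true 24-month prevalence, and rc and rn the retention in cases and non-cases.

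Observed prevalence = p·rc / [p·rc + (1 − p)·rn]; 95% half-width = 1.96·√[obs(1 − obs)/2527].

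The article gives only the overall 30% loss. The values of p, rc and rn below are assumptions, chosen so that overall retention is about 70%.

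1. p = 12%, rc = 55%, rn = 72%. Numerator 0.12 × 0.55 = 0.0660. Denominator 0.0660 + 0.88 × 0.72 = 0.6996. Observed 9.4%. Half-width 1.96 × √(0.0943 × 0.9057/2527) = 1.1 points. The bias of 2.6 points is more than twice the half-width.
2. p = 12%, rc = 60%, rn = 71%. 0.0720 / (0.0720 + 0.6248) = 10.3%. Half-width 1.2 points, bias 1.7 points.

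**Same check by dropout ratio.** Hold overall loss at 30% and let k be the ratio of dropout in cases to dropout in non-cases. Then dropout in non-cases is d0 = 0.30/(1 − p + k·p), dropout in cases is k·d0, and the observed prevalence is p(1 − k·d0)/0.70.

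| True p | k (assumed) | Observed | Bias, points | Half-width, points | Coverage of the 95% interval |
|---|---|---|---|---|---|
| 24% | 1.25 | 22.2% | 1.8 | 1.6 | 39% |
| 24% | 1.5 | 20.5% | 3.5 | 1.6 | 1% |
| 10% | 1.25 | 9.1% | 0.9 | 1.1 | 62% |
| 10% | 1.5 | 8.2% | 1.8 | 1.1 | 8% |

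The 24% is the GAD prevalence cited in the article's Background; the 10% is an assumption. With k = 1 there is no bias. With k below 1 the bias is upwards.

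**GEE group contrast.** A two-visit binary outcome was simulated with about 30% dropout and illustrative settings. The second-visit odds ratio between groups was compared in all patients and in completers.

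| Dropout depends on | All patients | Completers |
|---|---|---|
| Group only | 1.50 | 1.50 |
| Earlier outcome only | 1.55 | 1.54 |
| Earlier outcome, differently by group | 1.56 | 1.29 |

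In the last case inverse-probability weighting brought the odds ratio back to 1.54.

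A second, five-visit simulation made dropout two to three times as likely after a bad value. True 24-month risks of 26.8% and 39.5% were read as 24–25.5% and 36–38%. The true odds ratio is (0.395/0.605)/(0.268/0.732) = 1.78. Pairing the lower ends gives (0.36/0.64)/(0.24/0.76) = 1.78, and the upper ends (0.38/0.62)/(0.255/0.745) = 1.79. The levels fall, but the contrast hardly moves.

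**The case against.** **Silence.** The article nowhere says that the estimates are unweighted, and it does not exclude weighting or imputation. A condensed article commonly leaves such detail to a fuller document. This stands: the absence of a missing-data section is not the point. The point is that the stated estimator, followed as written, is sensitive to a loss that the article itself expects, and that a better one is cheap.

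**The background sentence.** A reader might infer that the article links PD/GAD to dropping out of the study. It does not. The sentence concerns attendance at cardiac rehabilitation and use of medication, and anxiety levels rather than diagnoses. Study follow-up is also easier to complete, by phone, web or mail, with reminder calls and a prize draw. Even the direction is open: the Background also describes these patients as frequent users of medical consultations, who might be easier to retain. Diagnosis-related dropout is plausible, not stated.

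**GEE.** A reader might infer that GEE is valid only if dropout is completely random, so that any link between PD/GAD and dropout biases every dichotomous comparison. That is too strong. Group and many covariates are in the model, and the check shows no bias from group-related dropout and almost none in the contrast from dropout tied to the earlier outcome alone. Bias in the contrast needs dropout tied to earlier outcomes differently by group, or to new-onset PD/GAD.

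**Records.** Cardiac events and rehabilitation attendance can be taken from records without an interview. This largely protects them, although outside records need consent and the article still applies the 30% loss to objective 2a.

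**Limits of the remedy.** In the prevalence example retention depends on true 24-month status. Weighting on earlier status repairs that only so far as earlier data predict it. This also stands.

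**Conclusion.** The point holds for objective 1. Follow-up prevalence and incidence, presented visit by visit among those interviewed, are unbiased only if retention is unrelated to diagnosis. Inflating recruitment does not change this. The exposure is greatest at 24 months, where the expected loss is 30%; the article gives no loss for earlier visits.

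Modest differences in retention would be enough to matter. The bias exceeds the half-width at a dropout ratio of about 1.25 if prevalence is 24%, and at 1.5 if it is 10%. At 12%, retention of 55% against 72% gives 9.4%, and 60% against 71% gives 10.3%. All retention values are assumptions, and the article contains none by diagnosis.

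For objective 2 the point is limited to dichotomous outcomes taken from interviews or questionnaires (smoking, alcohol, physical activity), and to dropout patterns that the model covariates do not absorb. The documents do not support saying that the GEE comparisons are biased in general, or that the cardiac-event analysis is at comparable risk.

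This is an inexpensive improvement to the stated analysis. It does not show that the results will be wrong.

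**What to change.** For PD/GAD prevalence and incidence at each follow-up visit, and for GEE of visit-collected dichotomous outcomes, use inverse-probability-of-retention weighting or multiple imputation. Build either from data already collected at earlier visits: previous PD/GAD status, HADS score, adherence, previous values of the outcome, age and sex. Report the unweighted estimates alongside, so that the reader sees how much retention matters.

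State the assumption in the plan: the method corrects dropout explained by observed data, and not dropout that depends on a diagnosis arising after the last completed interview.

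The cost is analysis wording, modest programming and slightly wider confidence intervals. No new data are needed, and recruitment and visits are unchanged.

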## Methods

### Design

This is a prospective cohort study in which participants will be evaluated at 5 time points: baseline, 3 months, 6 months, 1 year and 2 years. The study was registered with clinicaltrials.gov (NCT04433832).

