#### Adverse cardiac events (objective 2a)

Patients will be asked about all potential adverse events occurring during the study period with a structured medical interview developed by our team [79, 80]. All data will be confirmed by an independent review of medical records. With written consent from patients or next of kin (if deceased), records for admissions or consultations outside of the study hospital will be obtained from the hospital archives. Medical data will be extracted using a combination of a standardized medical data extraction form known for its excellent reliability (Cohen’s k = 0.72–0.91) and modules from the GRACE initial form [79–81].

Adverse events are defined as: either an acute myocardial infarction as defined by the Joint ESC/ACCF/AHA/WHF Task Force for the Universal Definition of Myocardial Infarction [82], a revascularization procedure (percutaneous coronary intervention or coronary bypass grafting), a cardiac arrest (including ventricular fibrillation) or death from a cardiovascular cause (primary cause).

The main outcome for objective 2a is the presence of any of the listed adverse events. The association between the presence of PD or GAD and each individual type of event will also be explored.

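### Objective 2a is sized on a single relative risk, but the only contrast the article names for it is a group X time interaction, which is near zero if the relative effect is roughly constant over follow-up

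*Protocol article*

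**What the plan says.** *Objectives* asks for the association between PD or GAD and adverse cardiac events. *Adverse cardiac events (objective 2a)* defines one composite yes/no outcome: "The main outcome for objective 2a is the presence of any of the listed adverse events".

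*Justification of sample size* takes the total from this objective ("n = 2527 participants"). It uses "a previously reported rate of adverse cardiac events of 14.3"% and states that "the relative risk of adverse events in patients was conservatively estimated at 1.50". No time pattern is attached to that relative risk.

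*Statistical analyses* then gives one analysis for all dichotomous outcomes: "generalized estimating equation models (dichotomous outcomes) with group X time interactions will be used to compare the evolution of both groups". The comparison is of "both groups (with and without GAD or PD) in terms of adverse cardiac events", and the other objective 2 outcomes follow in the same list. No risk ratio, hazard ratio or group contrast over the whole follow-up is named. The later check for differences between men and women is written as a group X sex X time term.

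**The concern.** An association with any event over two years is a difference in level between two groups. A group X time interaction measures whether that difference changes over time. The study is sized for the first, and the article names the second.

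What is at stake is the objective that set recruitment at 3610. An analyst who takes the interaction as the test of 2a could report no significant effect while the planned 50% excess is present in the data. An analyst who reads the model differently could pick among several group contrasts after seeing the results.

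**Working it through.** **Inputs from the article.** Relative risk 1.50; event rate 14.3%; evaluable N 2527; attrition 30%; recruited 3610; assessments at "baseline, 3 months, 6 months, 1 year and 2 years", which give follow-up intervals of 3, 3, 6 and 12 months.

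**Assumptions.** The article does not give alpha, power, the share of patients with PD or GAD used in the sizing, or whether 14.3% is the overall or the unexposed risk. I use two-sided alpha 0.05, exposed shares from 10% to 24%, and both readings of 14.3%.

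**1. The article's own figure.** 2527 / (1 − 0.30) = 3610, which reproduces. The 2527 cannot be reproduced uniquely without the missing inputs, but it is in line with a plain two-proportion comparison. With 14.3% as the overall risk, 80% power and 10% exposed gives 2497; 90% power and 15% exposed gives 2501.

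**2. Power of a single group comparison at N = 2527.** Power = Φ{(|p1 − p0| − 1.96·SE0) / SE1}, where SE0 uses the pooled risk and SE1 the separate risks.

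Worked case: 14.3% as unexposed risk, 10% exposed.
- p0 = 0.143; p1 = 1.5 × 0.143 = 0.2145; difference 0.0715.
- n0 ≈ 2274; n1 ≈ 253; pooled risk 0.9 × 0.143 + 0.1 × 0.2145 = 0.150.
- SE0 = √[0.150 × 0.850 × (1/2274 + 1/253)] ≈ 0.0237.
- SE1 = √[0.143 × 0.857/2274 + 0.2145 × 0.7855/253] ≈ 0.0268.
- Power = Φ[(0.0715 − 0.0464)/0.0268] ≈ Φ(0.93) ≈ 82.5%.

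| Exposed share | 14.3% as unexposed risk | 14.3% as overall risk |
|---|---|---|
| 10% | 82.5% | 80.4% |
| 15% | 92.4% | 90.3% |
| 24% | 98.0% | 96.4% |

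**3. Size of the interaction under a constant relative risk.** On a log link the group effect is ln 1.50 = 0.405 in every interval, so the interaction is exactly 0. On a logit link, with 14.3% as unexposed risk spread evenly over 24 months:
- 3-month interval: risks 0.0179 and 0.0268; log odds ratio 0.41.
- 12-month interval: risks 0.0715 and 0.1073; log odds ratio 0.44.
- Cumulative to 24 months: risks 0.143 and 0.2145; log odds ratio 0.49.

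The drift is about 0.03 with interval coding and 0.08 with cumulative coding, against a group effect of 0.41-0.49.

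**4. Simulated rejection of the interaction at N = 2527.** Wald test on 3 degrees of freedom across the four follow-up points, 5000 runs per cell, constant relative risk 1.50:

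| Exposed share | Interval, logit | Interval, log | Cumulative, logit | Cumulative, log |
|---|---|---|---|---|
| 10% | 3.1% | 3.5% | 5.9% | 6.4% |
| 15% | 3.7% | 4.3% | 5.0% | 5.4% |
| 24% | 4.3% | 4.8% | 5.1% | 4.5% |

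All are at about the type I error level. A separate simulation with constant hazards and a logit model by interval gave about 3-4%.

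**The case against.** **The interaction is not stated to be the only test.** The article describes a model that contains interactions. Such a model also has group terms, and the trigger for the sex analysis speaks of significant effects of the disorders, not of significant interactions. Under constant hazards a joint test of the group terms across the four intervals rejects in about 72-94% of simulated studies. This stands: a reader might infer that the study would very likely report a null result for 2a, and the text does not support that. It does not remove the point. No group contrast is named, comparing how groups evolve is what an interaction does, and the sex effect is written as a modification of group X time. The joint test also has less power than the single comparison the study was sized for.

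**A relative risk of 1.50 at two years does not imply a constant effect.** This also stands, and *Anxiety and coronary artery disease* says that untreated PD and GAD worsen over time. With 14.3% v 21.45% at 24 months but the excess starting only after month 6, the interaction rejects in about 9% (10% exposed) and 36% (24% exposed). With all the excess in year 2 it rejects in about 41% and 83%. Even these late-effect cases fall short of the single group comparison.

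**No link is named.** On a risk-difference scale with cumulative coding, the change in risk difference from month 3 to month 24 does carry the effect, and rejects in about 69% and 95%. But the sizing is in relative risk, and nothing in the article points to that scale.

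**The detail belongs in the analysis plan.** Link, coding and covariates may. Here, however, the article itself fixes a contrast, and it is not the one that was sized.

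**Conclusion.** The mismatch is real for objective 2a and should be corrected. Under a roughly constant relative effect and a log or logit link, the named contrast has rejection rates of about 3-6%, against about 80% (10% exposed) to 96-98% (24% exposed) for the single group comparison at N = 2527. The contrast between these figures holds for every exposed share, event coding and reading of 14.3% tried. It weakens if the effect starts late, or if the analysis is on a risk-difference scale.

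Some stronger conclusions might be inferred but lack support:
- That the sample size is wrong. 2527 is consistent with the group comparison, and only the contrast needs to be named.
- That the same fault invalidates objectives 2b-2d. Comparing trajectories of repeated questionnaires is a legitimate choice, the article plans a repeat with 3-month diagnoses if remission is common, and no calculation was made for these outcomes.
- That deaths from non-cardiovascular causes are treated as missing data. The article only leaves them out of the composite.

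**What to change.** In *Statistical analyses*, state that the primary 2a contrast is the covariate-adjusted PD/GAD group effect on any adverse cardiac event over 24 months, reported with its 95% confidence interval. A risk ratio matches the sizing directly. A hazard ratio for time to first event is an alternative if event dates are available; the article describes extraction from medical records but does not mention dates. A Cox model on all 3610 patients is therefore one option, not a requirement. Make group X time a secondary analysis of whether the association changes over follow-up.

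The cost is wording: N need not change, and the risk-ratio version uses the outcome already defined. The small downside is that differential change over time becomes a secondary question.

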Diagnosing anxiety disorders such as GAD and PD in patients with CAD can be challenging as there is a significant overlap in the somatic symptoms of both conditions (e.g. chest pain, dizziness, dyspnea, palpitations and tiredness) [20, 21, 33, 35, 56]. This may explain why anxiety disorders have been found to be more prevalent in the few studies in which they were diagnosed using structured interviews (the gold standard for psychiatric diagnoses) conducted by trained mental health professionals [33]. Furthermore, a single assessment point, as was used in several reviewed studies, might not be reliable in order to adequately identify pathological anxiety in patients with CAD [20–22, 24, 25, 27, 31–33]. Indeed, some authors have expressed concerns that assessing anxiety disorders shortly after a cardiac or life-threatening event may lead to false positives [28, 35]. In addition, the onset of a chronic illness such as CAD and dealing with its consequences are risk factors for the development of GAD and PD [57] and could lead to an elevated incidence of these disorders in the following months and years. Thus, further prospective studies using validated structured interviews and a robust methodology to assess the prevalence and incidence of PD and GAD in patients with CAD are needed [33].

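### The exploratory three-group repeat sorts patients by diagnoses made during follow-up but analyses cardiac events over the whole study period, so it cannot show the effect of developing PD or GAD

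*Protocol article*

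**What the plan says.** All places are in the protocol article.

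- **Statistical analyses, main model.** Mixed models and GEE "with group X time interactions will be used to compare the evolution of both groups (with and without GAD or PD"). The fallback to 3-month diagnoses, should baseline diagnoses prove unstable, implies that the main groups are set at baseline.
- **Statistical analyses, last paragraph.** "All analyses will be repeated using 3 groups": PD or GAD at baseline, then "patients who developed PD or GAD afterwards, patients without PD or GAD at all time points". The purpose is "in order to explore the impact of developing GAD or PD over time". The paragraph is presented as exploratory. It states no time-updated exposure, landmark or lag.
- **Adverse cardiac events (objective 2a).** "Patients will be asked about all potential adverse events occurring during the study period". The composite includes "death from a cardiovascular cause (primary cause").
- **Anxiety and coronary artery disease (Background).** The authors note that "the onset of a chronic illness such as CAD and dealing with its consequences are risk factors for the development of GAD and PD".
- **Justification of sample size.** "Considering an anticipated attrition rate of 30% after 2 years".

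**The concern.** The second and third groups are defined by what happens after baseline, while the outcome is followed from baseline. For objective 2a, three distortions follow.

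1. **Immortal time.** A patient can enter the developed group only by being alive and interviewed at the diagnosing visit. A patient who dies at month 2 can never belong to it.
2. **Classing of deaths and drop-outs.** Absence of the disorder at every time point may mean that all five assessments were attended and negative, or that no attended assessment was positive. The first reading removes deaths and drop-outs from the reference group; the second leaves them in. The bias can change direction between the two.
3. **Reverse causation.** An infarction at month 4 followed by panic disorder diagnosed at month 6 counts as an event in the developed group. The Background itself gives the reason to expect this sequence.

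The repeat has an aetiological aim, and no other objective 2 analysis described isolates new-onset disorder. A relative risk away from 1 could arise with no effect of the disorder, and a larger sample would not remove it.

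**Working it through.** **Inputs from the documents.** Two-year event risk 14.3%; attrition 30% (the recruitment target reproduces: 2527 / 0.70 = 3610); visits at 0, 3, 6, 12 and 24 months; planning relative risk 1.50.

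**Assumptions, not in the documents.** Baseline PD or GAD 12%; onset 3% at each follow-up visit; 10, 20 or 40% of events fatal; 25, 15, 25 and 35% of events in the four visit intervals; drop-out uniform in time. The disorder has no effect on events.

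**Method.** Three million simulated patients per scenario. RR = two-year event risk in the developed group / two-year event risk in the never group. Two features that the text leaves open are varied: whether events after drop-out are still captured, and whether deaths and drop-outs stay in the never group or only completers count.

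| Fatal share | Events captured | RR, deaths and drop-outs kept in never | RR, never limited to completers |
|---|---|---|---|
| 10% | to 2 years | 0.95 | 1.05 |
| 20% | to 2 years | 0.90 | 1.10 |
| 40% | to 2 years | 0.80 | 1.27 |
| 10% | until drop-out | 1.03 | 0.99 |
| 20% | until drop-out | 0.97 | 1.03 |
| 40% | until drop-out | 0.85 | 1.19 |

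The null range is thus about 0.8 to 1.3. At 20% fatal, 48 to 50% of events in the developed group fell on or before the diagnosing visit.

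**Reverse causation.** Let an event double the probability of onset at the next visit (3% to 6%), at 20% fatal:

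| Events captured | Kept in never | Completers only |
|---|---|---|
| to 2 years | 1.08 | 1.34 |
| until drop-out | 1.17 | 1.26 |

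The range is about 1.1 to 1.3, and 57 to 59% of the developed group's events now fall on or before diagnosis.

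**Time-updated exposure on the same data.** Classing each patient by status at the start of each visit interval, and counting only events in that interval, gives a relative risk of 0.99 to 1.01 in every scenario, including reverse causation.

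**Sampling error for comparison.** About 8.6% of patients fall in the developed group: 0.086 × 3610 ≈ 310. The never group is about 0.88 × 3610 − 310 ≈ 2867. SE(log RR) = √[(0.857/0.143)(1/310 + 1/2867)] = √(5.993 × 0.003575) ≈ 0.146. The null 95% interval is exp(±1.96 × 0.146), about 0.75 to 1.33.

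**Limits.** The simulation uses a cumulative relative risk, not the planned GEE with group by time terms. Nothing was simulated for objectives 2b to 2d.

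**The case against.** The strongest reply is that this is an exploratory repeat. That stands, and it limits the severity: objective 1, the sample size and the main comparison by baseline diagnosis do not depend on it. A reader might infer that the study's principal answer on cardiac events is compromised; the documents do not support that.

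Second, the size depends on assumed inputs. This also stands. The null biases mostly lie inside the sampling interval of about 0.75 to 1.33, and some scenarios show almost none (1.03 and 0.99 at 10% fatal with capture until drop-out). The reverse-causation figures rest on an assumed doubling.

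Third, a reader might infer that the baseline group is also necessarily biased against the never group. With 20% fatal and full capture, that relative risk is 1.22 if the never group is limited to completers and the baseline group is not. It is 1.00 if deaths and drop-outs stay in the never group, and 1.01 if both groups are limited to completers. The text does not impose the asymmetric reading.

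Two replies do not hold. Group by time terms do not cure the fault, because the label still depends on later survival and diagnosis, so early intervals compare patients by their future. Nor is this merely detail left to an analysis plan: the article states the grouping rule, and that rule is what causes the problem. How deaths and drop-outs are classed may well be set elsewhere, but neither reading of it removes the fault.

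**Conclusion.** The point holds for the exploratory three-group analysis of objective 2a and should be fixed. As defined, that analysis cannot separate the effect of developing PD or GAD from immortal time, the classing of deaths and drop-outs, and events that precede the diagnosis.

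Under no effect, the developed-versus-never relative risk is about 0.8 to 1.3 across 10 to 40% fatal events, both capture rules and both readings of the never group. If an event doubles onset at the next visit, it is about 1.1 to 1.3 at 20% fatal. These figures show plausible size; they do not predict the result. The existence of the fault follows from the definitions, but its net direction cannot be foretold.

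For objectives 2b to 2d, the same grouping mixes outcomes measured before and after the diagnosis, but immortal-time arguments about events do not carry over directly. No size is claimed there.

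**What to change.** Replace the three fixed groups for objective 2a by a time-updated exposure. Status starts from the baseline interview and switches at the visit of first diagnosis. Only later events are attributed to the developed state; earlier follow-up stays unexposed. Patients who die or leave contribute until then. This fits the planned GEE if the data are arranged by visit interval, with exposure taken at the start of each interval. Under the Procedures, patients are interviewed and their records reviewed at each time point, so the interval of an event should be known even though the article does not say that event dates are extracted. A landmark analysis at one fixed visit, among patients alive and in follow-up, is a simpler alternative.

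For 2b to 2d, relate the diagnosis at one visit to the outcome at the next.

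The cost is a changed paragraph, moderately more programming and some precision. Onset first found at 24 months contributes no exposed follow-up and has no later outcome; under the assumptions above, that is about 19% of the developed group. No new data collection should be needed.
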